## Abstract

**Background:**

Large health inequalities exist in the Netherlands among individuals with a high compared to a low socioeconomic position. Worksite health promotion interventions are considered promising to reduce these inequalities, however, current interventions seem not to have the desired effects. This study proposes ‘moral case deliberation’, a form of stakeholder dialogue on moral dilemmas, as an integrated and inclusive intervention for worksite health promotion. This intervention takes into account three factors that are considered possible underlying causes of low effectiveness of current interventions, namely the lack of deliberate attention to: 1) the diverging values and interests of stakeholders in worksite health promotion, 2) the ethical issues of worksite health promotion, and 3) the connection with the lived experience (lifeworld) of lower SEP employees. Moral case deliberation will help to gain insight in the conflicting values in worksite health promotion, which contributes to the development of a vision for worksite health promotion that is supported by all parties.

**Methods:**

The intervention will be evaluated through Responsive Evaluation, a form of participatory research. Key to Responsive Evaluation is that stakeholders are consulted to determine relevant changes as a result of the intervention. The intervention will be evaluated yearly at both fixed moments (baseline and annual evaluation(s)) and continuously. Mixed methods will be used, including interviews, participatory observations, analyses of HRM-data and short questionnaires. In addition, the intervention will be evaluated economically, on both monetary and non-monetary outcomes.

**Discussion:**

This protocol proposes an innovative intervention and a novel participatory evaluation in the context of worksite health promotion. The study aims to gain understanding in how dialogue on moral dilemmas on health and health promotion can contribute to heightened personal and mutual understanding among stakeholders and practice improvements in the work context. By evaluating the intervention in more than one setting, findings of this study will provide knowledge about how MCD can be adapted to specific work settings and what changes it may lead to in these settings.

**Trial registration:**

Netherlands Trial Register (NRT): NL8051. Registration date: 28/09/2019, retrospectively registered. https://www.trialregister.nl/

## Background

Large health inequalities exist in the Netherlands between individuals with an high socioeconomic position (SEP) and individuals with a low SEP. Low SEP individuals are expected to live 7 years shorter than those with high SEP, and about 19 years shorter in good health [1, 2]. These SEP-related health inequalities can be explained by differences in conditions in the physical environment (e.g. housing and working conditions) and the social environment (e.g. social support), and by behavioural factors (e.g. lifestyle) [3]. Health inequalities are often discussed in terms of injustice: those who are already favoured in wealth also have better chances of being healthy [4]. Individuals with poor health have less opportunities to live their life as they want to, because their health situation may impede social, economic or societal participation. Besides that, poor health is associated with higher societal costs [4], and decreased economic productivity in organizations [5]. In 2014, approximately 20% of Dutch individuals aged 25 and older had a low SEP [6]. Hence, it is warranted from an individual, organisational and societal perspective, to explore ways to promote health among low SEP individuals.

Worksite health promotion (WHP) is considered promising to promote health among lower SEP employees for two reasons. First, because the worksite gives access to the generally hard to reach low SEP population, as half is employed [7] and employees spend much time of their lives at work [8, 9]. Second, because the workplace facilitates an integrated or ‘social ecological’ approach for health promotion by allowing to target a combination of both individual and contextual factors that influence health [10], such as working conditions, social support and lifestyle [3]. Thus, the work setting can be enabling and facilitating for integrated approaches of health promotion to promote health of lower SEP employees.

Yet, current literature gives reasons to doubt on whether WHP interventions in their current form can reduce health inequalities. A meta-analysis [11] showed that WHP interventions that include a cognitive and educational component are more effective in promoting healthy lifestyle for higher SEP employees than for lower SEP employees. Also, a systematic review showed that WHP interventions focusing on health education were ineffective in decreasing socioeconomic health inequalities [12]. Moreover, a summary of literature reviews on the effectiveness of WHP aiming at promoting healthy lifestyles of employees in general (rather than specific lower SEP employees), concludes that WHP interventions have positive, but small effects overall [13]. Consequently, it has been questioned whether these small effects are the result of the intervention itself (theory-failure), or of the way interventions are implemented or evaluated (programme failure) [14]. Therefore, it is warranted to look at the possible underlying causes of the small effects of WHP for employees in general, and for the even smaller effects for lower SEP employees in particular.

A first underlying reason for low effectiveness in general might be the lack of acknowledgement of diverging values and interests of the many stakeholders that are involved in WHP. Stakeholders such as the employer, employees, intervention providers, research and knowledge institutes and insurance companies, all have their own interests regarding WHP [15]. For example, employers may want to promote employees’ health for cost-saving aspects, sustainable employability in the light of aging workforce, and good employment practice for company image building. Intervention providers at their turn want to sell their programs to employers, as that is how they derive their reason of existence [16]. For employees however, it is not self-evident that they receive WHP programs with open arms [17]. Employees go to work to for example earn a living, develop themselves, build on meaningful work relations with colleagues, and/or contribute to something valuable [18], but not necessarily to get their health promoted [19]. Interventions should pay attention to this multiplicity of values and interests at stake.

Following on this is the second possible underlying cause for small effects in general, which is the lack of awareness about the ethical side of WHP. Employees can experience WHP interventions as interference in their privacy, which in its turn can a play role in employees’ decision whether to or not to participate [20]. On the other hand, as employees depend on their employer to maintain their job, employees might feel coerced to participate in WHP interventions [16]. Also, questions such as how far an employer can go in promoting employees’ health often rises [20] as well as whether (and to what extent) employees are responsible for their health or whether their employer is [19]. To conclude, it is important to take into account the ethical questions and the conflicting values that come along with WHP, as they can influence participation in WHP and the relationships at the workplace.

A third possible reason for low effectiveness in general is that employees generally lack voice in WHP [19]. This is considered of particular importance for lower SEP employees because, although there is ample knowledge about the health issues that lower SEP employees generally face (e.g. unhealthier lifestyle or poorer working conditions), insight is scarce in how these people experience their work and health promotion interventions, and how to target their health effectively considering their lifeworld [13]. The possible influence of lifeworld, as conceptualized by Habermas [21], on WHP can be found in a qualitative study among low SEP individuals [22]. These individuals indicated they were aware of the negative consequences of certain health behaviours, yet changing these behaviours had no priority due to other problems in their lives for which they indicated to ‘need’ certain types of unhealthy behaviours. Similar patterns may be seen in WHP: lower SEP employees may find health and health promotion important, yet the specific work setting they are in as well as their personal situation may make them feel powerless or not interested to improve their health.

This project proposes an intervention that takes into account the aforementioned possible underlying causes, which together all add to the complexity of WHP. The intervention consists of stakeholder dialogues on moral dilemmas and underlying values, in which various stakeholders of WHP are invited to discuss health and health promotion. Lower SEP employees play a central role in the dialogues, to make sure that health is being discussed from their lifeworld’s perspective. A form of stakeholder dialogue that allows to take into account the aforementioned ethical dimensions of WHP is moral case deliberation (MCD) [23]. MCD is a form of stakeholder dialogue that originates from philosophy, with a theoretical background in pragmatic-hermeneutical and dialogical ethics [23]. The aim of MCD is to create a moral learning process, by bringing together and confronting diverging perspectives and sorting out underlying values and norms. By creating a moral learning process with various stakeholders about moral issues related to health and health promotion, MCD aims to enhance the personal and mutual understanding and support for WHP, in which moral dilemmas have been taken into account. This may lead to for example improved working relations and mutual understanding among stakeholders on short-term, to enhanced experience of control and autonomy of employees on medium term and to an improved perception of health and well-being on long-term.

The type of evaluation of this project, Responsive Evaluation, will be supportive in adapting MCD to the context of WHP, in which it has not been used before. Stakeholder participation is the starting point of Responsive Evaluation, allowing stakeholders to be consulted about their ideas, needs and wishes regarding the adaptation of MCD to their work setting. Responsive Evaluation is a form of interactive, participatory research, making use of mixed methods [24] and aims to heighten the personal and mutual understanding of multiple stakeholders through dialogue, as the first step towards practice improvement. In Responsive Evaluation stakeholders are involved in the research process by formulating research objectives and relevant changes in consultation with them, and by continuously keeping stakeholders updated about findings during the research process. Additionally, Responsive Evaluation pays attention to silenced groups, such as employees in WHP, facilitating to take the lived experiences of lower SEP employees as the starting point for evaluation. Thus, the intervention and evaluation in this study are not isolated, but complementary and grounded in similar epistemological assumptions on the co-creation of knowledge [25].

## Objectives

Develop an integrated worksite health promotion intervention consisting of moral case deliberation to discuss moral issues related to health and health promotion.Evaluate the implementation of and changes due to moral case deliberation in the context of worksite health promotion, and the adaptations needed to make moral case deliberation relevant for the context of work health promotion and its stakeholders.Evaluate the economic impact of moral case deliberation as an intervention for worksite health promotion on economic outcomes, both monetary (Budget Impact Analysis) and non-monetary (Social Return on Investment).

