### Aim 2: Evaluate the implementation of and changes due to MCD

#### Study design

A Responsive Evaluation design will be used to evaluate the implementation and the eventual changes due to MCD. As described before, Responsive Evaluation is characterized by stakeholder involvement, yet the degree of involvement may range from collaborative evaluation, participatory evaluation and empowerment evaluation [27]. The evaluation in this project has the ‘lightest’ degree of participation, namely collaborative evaluation. In collaborative evaluation, stakeholders are consulted and involved in the evaluation, but the evaluator remains in mainly in charge of the decisions, thus power.

The implementation and impact of the intervention will be evaluated both at fixed moments as well as continuously. The fixed moments are at the beginning of the project (baseline) and a yearly evaluation. The minimum duration of the intervention is 1 year, with a maximum of 2 years. The baseline and yearly evaluation comprise mixed methods such as interviews, participatory observations and analyses of HRM-data. Continuous evaluation comprises participatory observations and short questionnaires. Figure 1 provides a schematic overview of the Responsive Evaluation. The overview includes the economic evaluation (aim 3).

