## Discussion

This paper describes the study protocol of the development and evaluation of moral case deliberation (MCD) as a worksite health promotion (WHP) intervention. MCD was chosen as a form of stakeholder dialogue because it pays attention to the multiplicity of values and interests in WHP and moral dilemmas at stake, employees’ lived experiences and power asymmetries in the work context. Responsive Evaluation was proposed as the type of evaluation of this study. This study will add to the current body of literature of WHP, as it provides a novel intervention as well as an original type of evaluation in the field of WHP.

The strength of this study is that Responsive Evaluation allows to respond to the dynamic and ambiguous context of the work setting. Organisations are constantly changing due to internal and external developments, which also changes the context in which WHP interventions are being performed. In order to maintain appropriateness of the intervention in a changed situation, Responsive Evaluation as well as the intervention offer the flexibility to adapt research goals and activities during the research process [24]. Ambiguity in the work setting is a result of power relations such as the dependency relationship between employer and employee. These power relations are also reflected in WHP, where the employer is in charge and the employee has little or no voice in WHP. The starting point of Responsive Evaluation is a bases of equality among various stakeholders [24, 34], as well as special attention to silenced voices such as employees in WHP, which makes this type of evaluation very suitable for the work setting.

To date, Responsive Evaluation is considered innovative in the field of WHP, where a Randomized Controlled Trial (RCT) is the gold standard. A RCT aims to evaluate causality by randomizing participants in an intervention and control group, and correcting for bias in the analysis [35]. One important difference between both types of evaluation is that Responsive Evaluation does not aim to evaluate causality. Instead, Responsive Evaluation aims to support the stakeholders in the setting under study to better understand their context themselves, which allows and supports them to make relevant practice improvements.

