Responsive Evaluation results in context-specific outcomes. In the field of social sciences and health promotion, there have been discussions about the external validity of such context-specific outcomes [34, 36, 37]. In her commentary, Carminati (2018) [37] proposes transferability as an alternative term for generalizability for research that comprises only or mainly context bound data instead of quantitative data. Transferability means that outcomes of a study can be ‘transferred’ to other contexts by the readers through extrapolation and application of the ‘thick description’ of the findings [24, 37]. In this project, findings will provide organisations and researchers knowledge about how MCD was adapted to two different work settings, and what changes MCD led to in those settings. To ensure quality of transferability in this study several measures will be taken [38], such as discussing findings’ resonance with existing literature from different settings.

In the present study, health inequalities associated with socioeconomic position (SEP) are the starting point of this study. We acknowledge that intersectionality between SEP and other social categories such as gender, age, ethnicity, disability and first language, also influence chances on good health and thus health inequalities, due to various factors [39, 40]. The intersection between social categories should eventually be the starting point of interventions that aim to reduce health inequalities. Although the intervention and evaluation method of this study allows to adapt to the context of an organisation, including its population, it can be questioned whether diversity in all its facets is optimally taken into account, as the main focus is on SEP.

Additionally, WHP interventions alone cannot reduce SEP related health inequalities, as only half of the low SEP population is working [7]. This means that the other half does not have a job and therefore cannot be reached through the work setting. Moreover, these low SEP individuals do not profit from the positive effects of work on health and general well-being [41]. Therefore, these non-employed low SEP individuals presumably deal with poorer health conditions than employed lower SEP employees. Therefore, it is highly recommended to develop health promotion interventions, which may include dialogue methods as well, for non-employed low SEP individuals through other settings.

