This protocol describes the development and evaluation of a worksite health promotion intervention consisting of moral case deliberation. The findings of this study may contribute to the body of literature about worksite health promotion and health inequalities, by evaluating moral case deliberation in two different work settings. Also, this study will provide novel insights into the suitability of Responsive Evaluation in worksite health promotion as an alternative to RCT. The results of this study are expected to be available in 2021–2022.

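### Objective 2 and the promised findings attribute changes to moral case deliberation, though the protocol says its evaluation design does not aim at causality; the uncontrolled HRM analysis is the most exposed

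*Protocol article*

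**What the plan says.** Three places in the protocol article use the language of effect.

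- **Objectives**, second objective: "Evaluate the implementation of and changes due to moral case deliberation in the context of worksite health promotion".
- **Aim 2, Study design**, which ties that target to a method: "A Responsive Evaluation design will be used to evaluate the implementation and the eventual changes due to MCD".
- **Discussion**, on transferability: the findings will tell organisations and researchers how MCD was adapted "and what changes MCD led to in those settings".

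One place disclaims that language. The **Discussion**, comparing the approach with a randomised trial, says: "One important difference between both types of evaluation is that Responsive Evaluation does not aim to evaluate causality".

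Other sections bear on the point:

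- **Study population**: the intervention is implemented in two organisations, and all employees may take part.
- **Change evaluation**: the goal is insight into changes as stakeholders perceive them.
- **Data analysis, Qualitative data**: the annual analysis looks first for the existence of changes and then for underlying mechanisms.
- **Data analysis, Quantitative data**: HRM indicators are followed over time and analysed by longitudinal multilevel regression, with a focus on lower SEP employees.
- **Budget impact analysis**: costs are compared with baseline each year, and any change is set against the investment in MCD.
- **Data for SROI**: the extent to which the intervention contributed to the outcomes is collected as percentages.

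**The concern.** The protocol gives a question about effects to a design that it says does not address effects. For the HRM indicators, a reader of the eventual report could not tell whether a stated change is simply a change over the period or a consequence of MCD. The Discussion expects readers to transfer the findings to other workplaces, so the distinction matters: an employer would read a change that MCD 'led to' differently from one that happened while MCD was running. A shift in job satisfaction, the article's own example of an HRM indicator, could be credited to MCD when a reorganisation or some other development produced it.

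**Working it through.** No arithmetic applies. The article gives no sample size, error rate or effect size, and the point depends on none. The check sets the statements side by side.

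**1. Does the disclaimer reach Objective 2?** The Discussion disclaims causality for Responsive Evaluation as a method. The Study design section under Aim 2 names Responsive Evaluation as the means of evaluating changes due to MCD. The disclaimer therefore applies directly to that part of the objective.

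**2. Does the described design separate MCD from other influences?** Write the observed change in an HRM indicator in one organisation as

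observed change = contribution of MCD + contribution of everything else over the period.

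This is one observed quantity with two unknown parts. The second organisation also receives MCD, so it adds one more observed quantity and two more unknowns. The multilevel model handles the grouping of employees and repeated measurement, but it does not split the sum. The lower SEP subgroup analysis does not supply an untreated comparison either, because higher SEP employees are not excluded from the intervention and are said to be able to benefit too.

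**3. Can the second term be taken as negligible?** The protocol says not. The Discussion gives continual internal and external change in organisations as a reason for choosing a flexible design. The intervention runs for one to two years, which leaves time for such change.

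**4. Which data are protected by other text?**

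| Data source | What it measures | Text that limits or supports attribution |
|---|---|---|
| Interviews and observations | Change as stakeholders perceive it | Change evaluation (perceived change); Qualitative data (mechanisms) |
| SROI outcomes | The stakeholder-perceived changes from the responsive evaluation | Data for SROI (percentage contribution) |
| HRM indicators | Change over time | None |
| Budget impact | Costs before and after | None |

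The first two rows have a reasonable reading as stakeholders' own accounts of what MCD did. The last two do not. HRM indicators are analysed as change over time by regression, and the budget impact is a before-after difference. Nothing carries the SROI percentages into either analysis.

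**5. Is the causal wording consistent?** No. The Discussion states the promised findings without a hedge, while the Abstract uses a conditional form for the same promise.

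**The case against.** The best defence is that the protocol largely says what it means by change. The Baseline section speaks of relevant changes according to the stakeholders, and the Change evaluation section speaks of perceived changes. The disclaimer comes straight after a description of how a randomised trial establishes causality, so it can be read as disclaiming counterfactual estimation only, with 'due to' standing for stakeholders' accounts. Evaluation without a causal aim is also a legitimate choice. This stands for the interview data. It does not stand for the HRM regression, and it leaves the wording of the objective, the design statement and the promised findings unchanged.

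A reader might infer several stronger criticisms, which the document does not support.

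- *That nothing in the plan links a change to MCD.* The SROI section collects contribution data, and its outcomes are the changes established in the responsive evaluation. The annual qualitative analysis also looks for mechanisms.
- *That the whole of Objective 2 is undermined.* The objective also covers implementation and the adaptations MCD needs, and neither depends on causal attribution.
- *That the closing paragraph makes an unsupported claim about randomised trials.* It offers only "novel insights into the suitability of Responsive Evaluation in worksite health promotion as an alternative to RCT". That is an outlook, it makes no causal statement about MCD, and using the method in two settings can yield such insights.
- *That the interviews need a formal rule before a change may be credited to MCD.* Attribution is already partly planned there, such a rule would be a matter of preference, and it would do nothing for the HRM data.

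**Conclusion.** The point holds as an inconsistency between what the protocol says it will conclude and what it says its design is for. It affects the change component of Objective 2 in three statements: the objective, the Aim 2 design statement and the promised findings in the Discussion. It has practical force mainly for the HRM indicators. The before-after cost comparison, reported under an objective about economic impact, needs the same caution. For stakeholder-reported changes the conflict is mild.

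No planned data collection or analysis is shown to be wrong, and the point is not a call for a control group or a randomised trial. It assumes that the article's description is complete on one matter, namely that no comparison group is used. The full protocol, if it differs, could change that. It could not remove the conflict between the article's objective and its Discussion.

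**What to change.** 1. In the Objectives, in the Study design section of Aim 2 and in the Discussion paragraph on transferability, replace 'changes due to' and 'led to' with: changes that stakeholders perceive as related to MCD, and changes observed over the period after its introduction.
2. In the Quantitative data section, state that changes over time in HRM indicators are descriptive and are not attributed to MCD. Say the same of before-after cost changes in the Budget impact analysis section.
3. Where the report discusses how far MCD contributed to a change, draw on the attribution data already planned for the SROI and say that this is the source.

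This is rewording only, with no new data, participants or analyses. The price is a more modest headline claim.
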